#### *11.7.1.16 Treatment of overdose*

An overdose is a dose in excess of the dose specified for each cohort in this CSP.

Overdosing is not likely to occur since all IMP will be administered by site personnel under medical surveillance. In cases of accidental overdose, standard supportive measures should be adopted as required.

An overdose should be documented as follows:

- An overdose with associated AE is recorded as the AE diagnosis/symptoms in the AE Log of the eCRF.
- An overdose without associated symptoms is only reported in the subject's medical records.

No known antidote is available.

### **11.7.2 Physical examination**

The physical examination will include assessments of skin (arms), lungs, cardiac, abdomen (liver and spleen).

### **11.7.3 Vital signs**

Systolic and diastolic blood pressure and pulse will be measured in supine position after 10 minutes of rest. Body temperature will be measured orally using a digital thermometer.

### **11.7.4 Resting 12-lead ECG**

Single 12-lead ECG will be recorded in supine position after 10 minutes of rest using an ECG machine. Heart rate and PQ/PR, QRS, QT and QTcF intervals will be recorded.

Safety ECGs will be reviewed and interpreted on-site by the Investigator.

### 11.7.5 *Laboratory safety assessments*

Blood samples for analysis of clinical chemistry, hematology and coagulation parameters will be collected through venipuncture or an indwelling venous catheter and sent to the certified clinical chemistry laboratory at Uppsala University Hospital and analyzed by routine analytical methods.

Urine analysis will be performed at the research clinic using dip sticks.

The following safety laboratory parameters will be assessed:

#### **Clinical Chemistry**

Alanine aminotransferase (ALT)

Alkaline phosphatase (ALP)

Albumin

Aspartate aminotransferase (AST)

Bilirubin (total)

Calcium

Chloride

Creatinine

Gamma-glutamyl transferase (GGT)

Glucose

Magnesium

Phosphate

Potassium

Sodium

Urea nitrogen

#### **Hematology**

Hematocrit

Hemoglobin (Hb)

Platelet count

Red blood cell (RBC) count

White blood cell (WBC) count w differential count

#### **Urinalysis (dip stick)**

Specific gravity

pH

Leucocytes

Nitrite

Protein

Glucose

Ketones

Urobilinogen

Bilirubin

Erythrocytes

#### **Coagulation**

Activated Partial Thromboplastin Time (APTT)

Prothrombin Complex International Normalized Ratio (PK[INR])

### 11.7.6 *Evaluation of local tolerability*

#### 11.7.6.1 *Evaluation of local tolerability by the Investigator and by independent evaluators*

The investigator and 3 to 5 independent evaluators will assess local tolerability reactions of each wound by direct inspection or by evaluation of photographs, respectively, at visits specified in Table 8.1-1 and Table 8.1-2. The following parameters will be evaluated per wound:

- Appearance of wound and wound edge (inflammation)
- Condition of skin surrounding the wound (inflammation)
- Hemorrhage
- Amount of exudate present
- Presence of slough/necrotic tissue
- Presence of granulation tissue
- Hypergranulation

Each parameter will be scored using a 4-graded scale (0-3). Details are provided in a separate document.

Each wound will be separately evaluated and the outcome will be documented in the eCRF.

Hemorrhage, but not coagulated blood in wounds, evident after IMP administration will be reported as an AE. Hemorrhage/bleeding apparent at several visits will be reported as intermittent bleeding.

Exceptional and persistent inflammation associated with the wounds will be reported as an AE as will any wound infection.

Other local tolerability parameters assessed by the Investigator and by independent evaluators will not be reported as AE.

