| If 2 subjects on active treatment have severe, non-serious AEs assessed at least possibly related to the IMP administration (independent of within or not within the same System organ class [SOC]) | 
 
1. Stop dosing of subjects with severe, non-serious potential ADRs.
 
2. If the AEs are clearly associated with a single, or multiple wound(s): unblinding of these wounds. Only voting members of the iSRC will be unblinded.

If the etiology of the AEs is not obviously associated with a single, or multiple, wound(s), no unblinding will be performed. The AEs will be regarded as related to ILP100-DP.
 
3. Evaluation by iSRC. The iSRC makes recommendation to Sponsor.
 
4. Sponsor decides how to proceed:

Both subjects meet stop criterion: stop further dosing at this dose level for all subjects. Sponsor decides if the study will be terminated or if dosing should commence at a lower dose level or at an intermediate dose level.
 
 |
| If 2 subjects in different cohorts have SAEs assessed as at least possibly related to IMP administration                                                                                            | 
 
1. Stop dosing of subjects with potential SADR.
 
2. If the SAEs are clearly associated with a single, or multiple wound(s): unblinding of these wounds. Only voting members of the iSRC will be unblinded.

If the etiology of the SAEs is not obviously associated with a single, or multiple, wound(s), no unblinding will be performed. The SAEs will be regarded as related to ILP100-DP.
 
3. Evaluation by iSRC. The iSRC makes recommendation to Sponsor.

Both subjects meet stop criterion: Termination of study.
 
                                                                                                                                                                                                                                      |

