#### 11.7.1.1 *Definition of adverse event*

An AE is any untoward medical occurrence in a clinical study subject administered a pharmaceutical product and which does not necessarily have a causal relationship with this treatment. An AE can therefore be any unfavorable and unintended sign (including clinically significant abnormal values from relevant tests, such as clinical safety laboratory tests, ECGs, vital signs), symptom, or disease temporally associated with the use of an IMP, regardless of whether it is considered related to the IMP.

Local bleeding and mild, transient inflammation in the wound area are common and expected reactions following skin biopsy. Therefore, bleeding and/or mild, transient inflammation observed during the early local tolerability evaluations, and when judged by the Investigator to be caused by a study procedure performed pre-treatment (i.e. due to biopsy) is reported as procedure-related in the eCRF. Bleeding, inflammation and infection assessed as non-procedure related will be reported as AEs.

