#### *11.7.1.7 Assessment of severity/intensity*

The grading of the severity/intensity of AEs will follow the CTCAE v5.0. Grade refers to the severity of the AE. The CTCAE displays Grades 1 through 5 with unique clinical descriptions of severity for each AE based on this general guideline.

The Investigator must assess the severity/intensity of an AE using the following definitions, and record it on the AE Log in the eCRF:

|                |                                                                                                                                           |
|----------------|-------------------------------------------------------------------------------------------------------------------------------------------|
| Grade 1 | Mild; asymptomatic or mild symptoms; clinical or diagnostic observations only; intervention not indicated.                                |
| Grade 2 | Moderate; minimal, local or non-invasive intervention indicated; limiting age-appropriate instrumental activities of daily living (ADL)*. |

|                |                                                                                                                                                                           |
|----------------|---------------------------------------------------------------------------------------------------------------------------------------------------------------------------|
| Grade 3 | Severe or medically significant but not immediately life-threatening; hospitalization or prolongation of hospitalization indicated; disabling; limiting self- care ADL**. |
| Grade 4 | Life-threatening consequences; urgent intervention indicated.                                                                                                             |
| Grade 5 | Death related to AE.                                                                                                                                                      |

*\*Instrumental ADL refers to preparing meals, shopping for groceries or clothes, using the telephone, managing money, etc.*

*\*\*Self- care ADL refers to bathing, dressing and undressing, feeding self, using the toilet, taking medications, and not bedridden.*

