#### 11.7.1.8 Assessment of causal relationship

The Investigator must assess the causal relationship between an AE and the IMP using the definitions below and record it in the AE Log of the eCRF:

- *Unlikely* – the AE has no temporal relationship to the IMP or is due to underlying/concurrent illness or effect of another drug (that is, there is no causal relationship between the IMP and the AE).
- *Possible* – the AE has a suggestive temporal relationship to the IMP, and an alternative etiology is equally or less likely
- *Probable* – the AE has a strong temporal relationship to the IMP or recurs on re-challenge, and another etiology is unlikely or significantly less likely

An AE is considered causally related to the use of the IMP when the causality assessment is *probable* or *possible*.

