#### 11.7.6.2 *Evaluation of local tolerability by the subjects*

The subjects will be asked to assess pruritus and pain on a 4-graded scale (0-3) of each wound.

Each wound will be separately evaluated and the outcome will be documented in the eCRF.

Persistent pain and pruritus reported by a subject may be reported as an AE, as judged by the Investigator.

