#### 17.5.6 *Local tolerability*

The following parameters are will be measured for local tolerability:

- Appearance of wound and wound edge (inflammation)
- Condition of skin surrounding the wound (inflammation)
- Hemorrhage
- Amount of exudate present
- Presence of slough/necrotic tissue
- Presence of granulation tissue
- Hypergranulation

Each variable will be presented using frequency tables by cohort, treatment and visit.

Shift tables will also be presented by cohort, treatment and visits if considered appropriate.

Subject assessment of pruritus and pain will be analyzed as above.

All data will be listed by cohort, treatment and subject.

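### Section 11.7.6.1 keeps slough/necrotic tissue and hypergranulation out of AE reporting at any score, in conflict with the AE definition in 11.7.1.1

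*Protocol*

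**What the plan says.** Section 11.7.6.1 lists seven parameters that the Investigator and the independent evaluators score per wound on a 0-3 scale; the score definitions are in a separate document. Hemorrhage evident after dosing is an AE. For inflammation and infection the rule is: "Exceptional and persistent inflammation associated with the wounds will be reported as an AE as will any wound infection". The section closes with: "Other local tolerability parameters assessed by the Investigator and by independent evaluators will not be reported as AE".

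Section 11.7.6.2 treats the two subject-rated items differently: "Persistent pain and pruritus reported by a subject may be reported as an AE, as judged by the Investigator".

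The general definition in Section 11.7.1.1 is broad: "An AE can therefore be any unfavorable and unintended sign". Its wound-specific paragraph names only bleeding, inflammation and infection.

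Severity and causality attach to AEs: "The Investigator must assess the severity/intensity of an AE using the following definitions" (11.7.1.7) and "The Investigator must assess the causal relationship between an AE and the IMP" (11.7.1.8). The local tolerability scores have their own analysis in Section 17.5.6: "Each variable will be presented using frequency tables by cohort, treatment and visit".

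**The concern.** The product is a topical living organism given to humans for the first time, and Section 8.4.1 predicts very low or undetectable systemic exposure of CXCL12. Damage at the wound is therefore the most relevant toxicity to look for. Of the findings that the closing sentence of 11.7.6.1 excludes, exudate and granulation tissue are ordinary features of an open wound. Marked necrosis and hypergranulation need not be.

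The protocol sets a threshold for inflammation and allows judgement for pain and pruritus, but gives neither to these two findings. An Investigator who reports a marked case under 11.7.1.1 breaches 11.7.6.1, and one who obeys 11.7.6.1 under-reports against 11.7.1.1. At stake is whether such a case enters the AE system, with its grading, attribution, follow-up and escalation rules.

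**Working it through.** The plan states no figure to reproduce. The check sets the reporting rules side by side and then counts the wounds covered.

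**AE route of each scored local reaction (11.7.6.1 and 11.7.6.2)**

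| Scored item | Rater | AE route |
|---|---|---|
| Wound and wound edge (inflammation) | Investigator, evaluators | Yes, if exceptional and persistent |
| Surrounding skin (inflammation) | Investigator, evaluators | Yes, same threshold |
| Hemorrhage | Investigator, evaluators | Yes, if evident after dosing (coagulated blood excepted) |
| Exudate | Investigator, evaluators | None |
| Slough/necrotic tissue | Investigator, evaluators | None |
| Granulation tissue | Investigator, evaluators | None |
| Hypergranulation | Investigator, evaluators | None |
| Pain | Subject | If persistent, Investigator's judgement |
| Pruritus | Subject | If persistent, Investigator's judgement |

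Items scored: 7 + 2 = 9. With a route: 2 + 1 + 2 = 5. Without one: 9 - 5 = 4. Setting aside exudate and granulation tissue as ordinary wound features leaves 4 - 2 = 2. No score, duration or clinical-significance exception applies to these two, so the result does not depend on how the 0-3 scale is defined.

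**What follows from not being an AE**

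- Severity (11.7.1.7) and causality (11.7.1.8) are assessed for AEs, so a marked case has neither.
- The duty to follow an event to resolution or the end-of-study visit (11.7.1.14) applies to AEs.
- The AE summaries (17.5.1) omit it.
- Every row of Table 8.4-1 is framed in AEs or SAEs, and an SAE is itself defined as a type of AE (11.7.1.2). The third row, for example, begins: "If 2 subjects on active treatment have severe, non-serious AEs assessed at least possibly related to the IMP administration". A finding that is not an AE cannot count there.

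**Wounds covered (9.3, 8.1.1, 8.1.2)**

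- SAD: 12 subjects x 4 wounds = 48, of which 12 x 2 = 24 active.
- MAD: 24 subjects x 8 wounds = 192, of which 24 x 4 = 96 active.
- Total: 48 + 192 = 240, of which 24 + 96 = 120 active.
- Day 3 biopsies in the SAD part remove one wound per arm: 12 x 2 = 24 wounds, 12 of them active. Remaining: 240 - 24 = 216, of which 120 - 12 = 108 active.

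These are ceilings on exposure to the rule. They are not estimates of cases.

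**The case against.** The strongest reply is that nothing is hidden. The incidence of local reactions, naming both findings, is itself a primary endpoint. Each wound is scored at 5 SAD and 12 MAD treatment-phase visits (Visits 2-6 and 2-13) and tabulated by treatment. The AE summaries in 17.5.1 are by cohort and overall with no treatment split, and every subject receives both active and control. For comparing active with control wounds, the tolerability tables are therefore the better source. The iSRC must review tolerability data before each escalation (8.4.3) and may act on trends outside the stopping criteria (8.4.1). Infection, hemorrhage or exceptional inflammation accompanying necrosis is still an AE. A specific rule may legitimately narrow a general definition, and some slough can be part of normal healing.

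Most of this stands. A reader might infer that marked cases go unrecorded, ungraded or unseen by those deciding on escalation. The documents do not support that: the 0-3 score remains, and only the CTCAE grade and the other AE consequences are missing. Nor do they support treating the stopping rules as seriously weakened, since a Grade 3 event in a 6 mm wound would be rare.

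The reply does not remove the inconsistency. Frequency tables carry no causality assessment and no follow-up duty. Concern about double recording carries little weight, because Section 11.7.7 already enters infections in both the tolerability module and the AE log. Section 11.7.1.10 covers AEs that the Investigator observes, and one could argue that the exclusion reaches the score but not a separate diagnosis; 11.7.6.1 draws no such distinction. The physical examination includes the skin of the arms, but after dosing it is first scheduled on Day 14 (SAD) and Day 32 (MAD). The iSRC's escalation data run to Day 3 and Day 21.

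**Conclusion.** The point holds as a reporting gap of limited size. Two of the seven parameters rated by the Investigator and evaluators can be pathological yet have no route to AE status at any score, which conflicts with 11.7.1.1. Calling these two potentially pathological, and exudate and granulation tissue ordinary, is a clinical judgement that the protocol does not make explicitly.

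A marked case stays visible in a primary endpoint and to the iSRC. It lacks a CTCAE grade, attribution and AE follow-up, is absent from the AE counts, and has no standing under Table 8.4-1.

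A reader might want to multiply the wound count by an assumed rate to obtain a number of missing AEs. The documents give no rate of marked necrosis or hypergranulation in these wounds, and the minipig study reported no treatment-related local toxicity. Manifestations of one condition are also recorded under a single diagnosis (11.7.1.11), so wounds do not convert one-to-one into AEs. The only supportable figures are the ceilings of 120 active wounds, and 108 after Day 3. The case for the change rests on the conflict in the text and on how little it costs to remove.

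**What to change.** Amend 11.7.6.1 so that slough/necrotic tissue or hypergranulation that is exceptional, persistent or clinically significant in the Investigator's judgement is reported as an AE, with severity and causality assessed. Keep the exclusion for exudate, granulation tissue and ordinary low-score findings. The threshold should be judgement rather than a score, because the score definitions are in another document; this also matches how the protocol handles pain and pruritus. The tables in 17.5.6 remain the place for the comparison by treatment.

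The change is one sentence. It needs no new visits, measurements or committee, since the wounds are already inspected and scored. The downside is a few more AE reports, some overlapping with the local tolerability tables.

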#### 11.7.6.2 *Evaluation of local tolerability by the subjects*

The subjects will be asked to assess pruritus and pain on a 4-graded scale (0-3) of each wound.

Each wound will be separately evaluated and the outcome will be documented in the eCRF.

Persistent pain and pruritus reported by a subject may be reported as an AE, as judged by the Investigator.

### 11.7.7 *Wound infections*

The Investigator will assess the wounds for any signs of infection such as smell or pus formation. Infections will be registered per wound in the local tolerability module of the eCRF as well as in the AE Log of the eCRF.

### **11.7.8 Assessment of CXCL12 anti-drug antibody formation**

Venous blood samples for the assessment of potential ADAs developed against CXCL12, will be collected through venipuncture or an indwelling venous catheter before the first administration and at visits outlined in Table 8.1-1 and Table 8.1-2.

The date and time of collection of each sample will be recorded in the eCRF.

The blood samples will be collected in pre-labelled K2-EDTA tubes and will be centrifuged at +4°C at 3000g for 15 minutes. The separated plasma from each sample will be divided into 2 aliquots in pre-labelled polypropylene cryotubes and frozen immediately at -70°C.

The samples will be analyzed by [REDACTED], by means of a validated ELISA or AlphaLisa method.

## **11.8 Assessments related to secondary endpoints**

### **11.8.1 Blood sampling for analysis of systemic exposure of CXCL12 in plasma and *L. reuteri* in blood**

Venous blood samples (approximately 5 mL) for the determination of plasma concentrations of CXCL12 (Section 11.8.1.1), for blood culturing (Section 11.8.1.2) for analysis of *L. reuteri* in blood, for future exploratory analyses (11.8.1.1) and for future PBMC analysis (Section 11.8.1.3), will be collected through venipuncture or an indwelling venous catheter at pre-specified visits (see Table 8.1-1 and Table 8.1-2). The blood samples will be collected in pre-labelled EDTA-K2 tubes.

The date and time of collection of each sample will be recorded in the eCRF.

On Day 3 and 14 of the SAD part (Visit 4 and Visit 5), and on Day 3, 5, 8, 15 and 21 of the MAD part (Visits 4, 5, 6, 9 and 12), 200 µL of the venous blood sample should be plated for blood culturing prior to centrifugation for plasma collection as described in Section 11.8.1.2.

#### **11.8.1.1 Plasma collection for CXCL12 analysis**

The collected samples should be placed on ice until centrifuged. Centrifugation will be performed at 4°C at 3000g for 15 minutes. The separated plasma from each blood sample will be kept on dry ice, divided into 3 aliquots in pre-labelled polypropylene Nunc cryotubes (polypropylene tubes with internal thread, Thermo Scientific, Denmark; A, B and C samples, 500 µL in each tube) and frozen at -70°C within 1 hour after collection. The A sample will be sent for analysis, the B sample will be kept as back-up and the C sample will be saved for potential future analyses of e.g. IgGs or levels of proteins associated with systemic inflammation or immune response.

The analysis will measure endogenous and bacterially-derived CXCL12 in the plasma samples using a validated method based on ELISA technology. The analysis will be performed by [REDACTED].

#### **11.8.1.2 Blood culturing for analysis of *L. reuteri* in blood**

A total of 200 µL of the venous blood sample (Section 11.8.1) will be transferred to 2 MRS +erm/vanco plates (100 µL to each plate) prior to centrifugation. Sterile glass balls (4 to 8) will be added and the blood will spread on the plates by gently shaking the plates back and

forth for 1-2 minutes. The plating must be done **before** centrifugation of the blood samples for collection of plasma.

The plates will be allowed to rest in room temperature with closed lids until all blood samples for the day has been taken. All plates will be placed in a jar, which in turn will be placed in an activated anaerobic bag that should be immediately closed. The jar will be placed in a 37 °C ( $\pm 2$  °C) incubator for 48 hours. After 48 hours the plates will be taken out of the jars and inspected for colonies.

Presence of absence of any colonies must be documented in the eCRF. In case of any colonies, the number of colonies per plate will be documented in the eCRF and the plate will be sent to [REDACTED] for subsequent evaluation. The colonies will be analyzed by [REDACTED] for viable *L. reuteri* R2LC containing the pSIP411 plasmid.

The data will be delivered as an external file.

